## Abstract

Background: Measurement-based care (MBC) is an evidence-based practice that incorporates routine outcome assessment using validated rating scales to guide collaborative clinical decision-making. Although MBC results in improved outcomes for patients with major depressive disorder (MDD), there are barriers to its broad implementation in clinical settings. The use of “enhanced” MBC (eMBC), with mobile apps that allow patients to track outcomes and engage in self-management via WeChat, may address some of these barriers. We hypothesize that implementation with eMBC using WeChat will be superior to standard MBC implementation using paper-pencil assessments at the clinic, for both implementation and clinical outcomes.

Methods: We present a trial protocol (clinicaltrials.gov NCT05527951) for a two-arm cluster randomized clinical trial (RCT) with a hybrid implementation-effectiveness design comparing standard MBC implementation versus eMBC implementation with a six-month follow-up in 12 mental health centers in Shanghai, China. The eMBC implementation uses a WeChat mini-program that includes outcome tracking using brief questionnaires and self-management lessons supplemented with support by a lay coach via WeChat.

Results: A total of 240 physicians and 1200 patients from the 12 mental health centers will be enrolled in the mixed-methods outcome analysis. The primary implementation outcome is *implementation reach*, defined as the proportion of eligible patients with a PHQ-9 score recorded in the hospital chart at six months after MBC implementation. The primary clinical outcome is *clinical remission*, defined as a PHQ-9 score of 4 or less at the six-month follow-up. Other implementation and clinical outcomes will be examined, including medication adherence, doctor-patient alliance, and a piggy-back cost-benefit economic analysis. Qualitative interviews will be conducted with physicians and patients to produce an interpretive account of the contextual factors that impact eMBC implementation.

Conclusions: The results of this hybrid implementation-effectiveness cluster RCT will inform implementation of eMBC with WeChat mobile apps for patients with depression in other clinical settings in China and internationally.

## Introduction

Major depressive disorder (MDD) affects more than 300 million people globally and is now the leading cause of disability and burden of disease worldwide [1]. Across the 36 largest countries in the world, more than 50 million years of lost productivity are attributable to depression and anxiety disorders every year, at an estimated cost of $925 billion [2]. On the other hand, scaled-up treatment of MDD can lead to large economic productivity gains of a net value of $230 billion. Despite known effective treatments for depression, fewer than half of those affected in the world (in many countries, fewer than 10%) receive such treatments [1]. Barriers to effective care include a lack of human and service resources, social stigma, and limited access to proper assessment, outcome measurement and monitoring, and evidence-based treatments, especially psychological treatments.

In China, depression is the second-most diagnosed disease (after heart disease) and costs the nation an estimated 52 billion yuan ($8.35 billion) every year [3]. China’s mental health care resources have developed quickly during the past three decades, but more growth is needed [4]. Most of the mental health resources, including psychiatrists and psychiatric inpatient beds, are concentrated within the larger cities, leaving the vast suburban and rural regions with few services for mental health treatment, and most psychiatric services in China still primarily serve patients with psychotic disorders. Yet, there are also indicators to suggest that China is primed to scale up in evidence-based practices. Many general hospitals have begun offering mental health services for patients with common nonpsychotic mood disorders such as MDD. Chinese guidelines for the treatment of MDD have been recently revised and the National Mental Health Work Plan 2015-2020 specifies improving the ability of healthcare facilities to identify depression and increasing the treatment rate by 50% [5].

Measurement-based care (MBC) - the routine use of simple, validated outcome scales such as the Patient Health Questionnaire (PHQ-9) depression scale [6] to guide clinical decision-making in treating MDD - is an evidence-based practice that may help meet these ambitious objectives [7]. The self-rated PHQ-9 can be helpful in screening, diagnosis and monitoring treatment; in primary care and other settings, the PHQ-9 can increase the recognition of MDD and improve outcomes when used within an MBC management approach [7]. For example, simple algorithms based on PHQ-9 scores can help physicians decide when to change the dose of an antidepressant or when to switch to another [7,8]. Importantly, it can help identify which patients are not improving so that more intensive treatment can be offered. MBC is shown to improve both clinical outcomes [9] and patient adherence to treatment [10], including in studies conducted in China [11], as summarized by meta-analysis [12]. However, despite recent policy-level recommendations for broad implementation of MBC [13,14] and recommendations in clinical practice guidelines [15], there is still a significant care gap in the implementation of MBC - only a minority of physicians and clinicians (in some studies, only 18% of psychiatrists and 11% of psychologists) use MBC in their clinical practice [16].

Study rationale

Implementation science has shown that adoption of an evidence-based practice like MBC by physicians and healthcare professionals is affected by many factors at various levels of organization [17]. In Phase 1 of the Enhanced Measurement-Based care Effectiveness for Depression (EMBED) study, we conducted a Situational Analysis addressing organization, clinician, and patient levels to determine the key barriers and facilitators for MBC implementation in Shanghai [18]. We found that, consistent with the literature [19,20], barriers include perceived time constraints, not knowing how to use measurement in clinical decisions, and challenges with integrating measurement into clinic workflow. We also found many facilitators to MBC implementation including positive attitudes about the clinical utility of MBC, interest in training in the use of scales, and beliefs that MBC would increase patient empowerment and reduce stigma [18].

Using the results from the Shanghai situational analysis [18], we adapted a standard MBC implementation plan [21] within an evidence-based framework, the Behavioural Change Wheel, that addresses contextual factors at administrative, organizational, clinician and patient levels [22]. The key elements of the EMBED MBC implementation plan (Appendix A) include support of hospital administration, identification of champions, clear policies, mapping of clinic workflow, MBC training for clinic doctors and administrative staff, adapting charts or electronic medical records (EMRs) for monitoring, and regular monthly MBC team consultation meetings.

The concept of enhanced MBC (eMBC), in which mobile health (mHealth) tools and services can engage both patients and physicians in using MBC, may also offer solutions to some of the identified barriers [7,23]. These enhancements include online or mobile apps for patients to monitor and track progress using validated self-rating scales such as the PHQ-9. The results from these app-based tools can then be shared with their physicians (e.g., by showing them the tracking charts or printing out the scores), thereby promoting a collaborative approach to MBC. The apps also have reminder systems (in-app notifications on mobile devices) so patients can be reminded to complete their questionnaires regularly (e.g., every two to four weeks) with messages to return to their physician (or other health provider) if their depression is not improving.

Enhanced MBC can also include interventional features such as Bounce Back, an evidence-based depression self-management [24] program delivered in Canada by the Canadian Mental Health Association [25]. Bounce Back was originally developed by [name] in the United Kingdom as primarily a self-help book supported by brief guided support [26]. Bounce Back consists of an online self-directed program based on cognitive-behavioural therapy strategies, supplemented with telephone support from a lay coach [25].

We have extended the concept of technology-enhanced mood measurement with the use of WeChat. WeChat is a Chinese multi-purpose messaging, social media and mobile payment app developed by Tencent that has become the world's largest standalone mobile app, with over 1 billion monthly active users in 2018. WeChat has been described as China's “app for everything” which provides text chats, video and audio conferencing, games, photo and video sharing, and other features [27]. WeChat Mini Programs are “mini-applications” built within the WeChat platform, developed by third-party companies to provide advanced features to users that can run within the app [28]. We have created a WeChat mini-program, which includes mood tracking and self-management lessons (similar to Bounce Back), to support eMBC.

In EMBED Phase 2, we will evaluate eMBC implementation using our WeChat mini-program by conducting a cluster randomized clinical trial (RCT) to compare the effectiveness of eMBC implementation versus standard MBC implementation in a real-world setting, i.e., mental health centres in Shanghai. The specific objectives for Phase 2 include: (1) To determine the incremental effect of eMBC over standard MBC on implementation and fidelity outcomes; (2) To determine the incremental effect of eMBC over standard MBC on clinical, health service and economic outcomes, and (3) To understand the contextual physician and patient mediators that affect eMBC implementation. We hypothesize that eMBC will outperform standard MBC on implementation, clinical, and health economic outcomes at both physician and patient levels.

A previous version of this article was posted at the Open Science Framework preprint server on August 26, 2021 (https://doi.org/10.31219/osf.io/9z82u).

## Materials and methods

This cluster-randomized trial is registered at www.clinicaltrials.gov [NCT05527951] in accordance with the policy from the International Committee of Medical Journal Editors [29]. The study protocol involves a two-arm cluster RCT with a hybrid implementation-effectiveness design [30] with a six-month follow-up. Using this design, we can compare the incremental benefit of eMBC over standard MBC for both implementation outcomes as well as clinical and health services outcomes.

We randomly allocated 12 mental health centres in Shanghai to two intervention groups (Figure 1). The unit of randomization was the mental health centre. We paired an urban centre with a rural centre to adjust for population size and to ensure a balance of urban and rural centres. A statistician blind to identity of the centres used a computerized program to randomly allocate each pair to control and experimental interventions in a 1:1 ratio. The centres allocated to the control intervention group will implement standard MBC using paper and pencil questionnaires [21] while those allocated to the experimental group will implement eMBC with our WeChat mini-program, *Easy to Recover from Depression*, which consists of mood tracking and lay-coached self-management (see Interventions). Once randomized, clinic centre staff and project personnel will not be masked to intervention assignment. Demographic and clinical measures will be collected from all participants via another WeChat mini-program called *eSmile*. The primary implementation outcome is Implementation Reach at six months, defined as proportion of eligible patients with a PHQ-9 score recorded in the chart or EMR, based on chart review. The primary clinical outcome is PHQ-9 remission (score ≤4) at six-month follow-up.

**Figure 1 FIG1:**
[figure not shown]
CONSORT diagram CONSORT, Consolidated Standards of Reporting Trials; MBC, measurement-based care; eMBC, enhanced measurement-based care.

Study design

We anticipate implementation in these 12 clinics with 240 physicians (about 20 per clinic). We will enroll 1200 eligible patients (about 100 per clinic) to assess clinical outcomes. The clinics allocated to standard MBC implementation will follow the implementation plan designed from EMBED Phase 1 (Appendix A). The implementation plan includes a package of validated outcome scales, standardized guidelines and algorithms for depression treatment based on adaptation of Chinese and Canadian Network for Mood and Anxiety Treatments (CANMAT) guidelines for MDD [15], MBC training workshops/webinars for physicians and staff, and monthly implementation meetings during the six months of follow-up. Clinics randomized to eMBC implementation will also be trained on the use of the *Easy to Recover from Depression* WeChat mini-program.

Study population

Study Sites

Of the 22 Shanghai community mental health centres, we identified 12 participating outpatient clinics from the Phase 1 situational analysis from the Hongkou Mental Health Centre, Fengxian Mental Health Centre, Songjiang Mental Health Centre, Xuhui Mental Health Centre, Changning Mental Health Centre, Nanhui Mental Health Centre, Yangpu Mental Health Centre, Qingpu Mental Health Centre, Pudong Mental Health Centre, Baoshan Mental Health Centre, Huangpu Mental Health Centre, and Putuo Mental Health Centre. These sites represent urban, suburban and rural regions of Shanghai. The Shanghai Mental Health Center will be the coordinating site for the study. Recruitment started at the Hongkou and Fengxian sites in January, 2023, with final site study visits anticipated to be completed in December, 2026.

Participants - Physicians

All doctors (n=20 per clinic, 240 total) working at each clinic will be involved in the MBC implementation. A sample of doctors (n=24) will be randomly selected for the qualitative interview assessments.

Participants - Patients

Because this is a pragmatic evaluation of an evidence-based practice, the eligibility criteria will be inclusive to ensure a broad representation of patients: (1) age 18 years and older; (2) diagnosis of unipolar depressive disorder made by the treating physician based on accepted diagnostic criteria (e.g., Chinese Classification of Mental Disorders (CCMD)-3, Diagnostic and Statistical Manual of Mental Disorders (DSM)-IV, DSM-5, International Statistical Classification of Diseases and Related Health Problems, 10th Revision (ICD-10)). A sample of patients (n=100 per clinic, 1200 total) will be selected to complete comprehensive clinical assessments (see Outcomes) via a WeChat research outcomes mini-program (called *eSmile*), which is separate from the eMBC *Easy to Recover from Depression* WeChat mini-program.

Interventions

Standard MBC Implementation

The standard MBC implementation is based on the EMBED implementation plan developed from the Situational Analysis tailored to the Shanghai context (for details, see Appendix A). In summary, the chosen MBC outcome measures include four brief, validated self-rated scales: PHQ-9 for depressive symptoms, Generalized Anxiety Disorder scale (GAD-7) [31] for anxiety symptoms, Sheehan Disability Scale (SDS) [32] for functioning, and the Frequency, Intensity, Burden of Side Effects Rating (FIBSER) [33] for medication side effects. These scales have been validated in Chinese populations [34-37]. The implementation plan includes workflow mapping to embed the scales and monitoring forms into clinic charts and workflow, e.g., flagging charts for patients with depression so that they receive the paper scales after registering for their clinic appointment and completing the scales while in the waiting room. The doctors will receive standardized training on MBC, including the use of scales and monitoring forms, how to discuss scores with patients, and simple treatment algorithms based on outcome measurement. Administration and clinical champions will be identified to lead the implementation and regular meetings with a consultation team will be held to collaboratively problem-solve implementation challenges.

Enhanced MBC (eMBC) Implementation

The eMBC implementation includes all the elements of the standard MBC implementation plan described, but patients will use the WeChat mini-program, *Easy to Recover from Depression*, instead of paper-pencil questionnaires at the clinic. The doctors and staff of clinics allocated to eMBC implementation will receive additional training on the *Easy to Recover from Depression* WeChat mini-program, which consists of the following two components.

Mood Measure:* *The *Mood Measure* component of the *Easy to Recover from Depression* mini-program consists of four scales to assess the symptoms of depression, functioning, and side effects of medications: PHQ-9, GAD-7, SDS, FIBSER. *Mood Measure* features include graphical display of scores, explanation of scores, graphical tracking of recent scores, and Frequently Asked Questions with answers. A scheduled reminder feature allows patients to set reminder notifications to complete the scales and through Print/Share function they can print or share the results.

Come Back:* *The University of British Columbia (UBC) and Shanghai Mental Health Centre (SMHC) teams have translated and culturally adapted the Bounce Back program for use in China, to be delivered via WeChat. The *Come Back* component of the *Easy to Recover from Depression* mini-program consists of six weekly lessons based on cognitive-behavioural therapy (CBT) principles. Each lesson includes an introductory video, narrated slides, a workbook, and worksheets to be completed by the patient. The six depression lessons include: (1) Understanding Low Mood and Depression; (2) Practical Problem Solving; (3) Doing Things That Boost How You Feel; (4) Noticing Extreme and Unhelpful Thinking; (5) Changing Extreme and Unhelpful Thinking; and (6) Understanding and Using Antidepressants.

In addition, patients using *Come Back* can connect with a coach via WeChat or telephone. The coaches are lay people who are trained to provide support and encouragement to complete the lessons. Coaches are available to patients for up to 20 minutes per week for six total sessions via chat, audio, or video link, depending on patient preference. Coaches are supervised via WeChat videoconference by a clinical psychologist based at Shanghai Mental Health Center. Fidelity will be assessed by the supervising psychologist using chart notes.

Ethics, security, and confidentiality

Ethics and Informed Consent

The study is approved by the Ethics Committee at the Shanghai Mental Health Centre (2020-77C2) and the Clinical Research Ethics Board at the University of British Columbia (H21-02581). Because both interventions involve implementation of an evidence-based practice, no individual consents are required for patients at each mental health centre. However, the selected patients for evaluation of clinical outcomes will provide informed consent via the WeChat *eSmile* research outcomes mini-program, assisted by research assistants at each site. In addition, patients and doctors selected for qualitative interviews will provide written informed consent.

Data Security and Confidentiality

All study data will be collected in China. The UBC study team will only have access to de-identified data from the trial conducted in Shanghai. We will comply with Standard Operating Procedures for data safety, management, sharing, storage, and retention with reference to relevant legislation and guidelines in both Canada and China. Data will be stored in a secure site managed by the PI and study staff in China, and will be transferred to UBC through *UBC TeamShare*, a secure data sharing platform.

## Results

Outcomes

Enrollment in the study started at one site on September 15, 2022. We have completed enrolment in two study sites, are currently enrolling in four study sites, and will start enrolling in the other six sites in January, 2025. We anticipate that enrollment will be completed by December 31, 2025, final follow-up data will be collected by June 30, 2026, and results will be available by October, 2026.

This study will evaluate both implementation and clinical outcomes. The implementation outcomes (Table 1) are based on definitions proposed by Proctor et al. [38] and are assessed via chart/EMR review at six months after MBC implementation. The primary implementation outcome will be implementation ‘Reach,’ defined as the proportion of patients with a PHQ-9 score recorded in the chart or EMR.

**Table 1 TAB1:** Implementation outcomes, definitions, and measures. EBP, evidence-based practice; MBC, measurement-based care; PHQ-9, Personal Health Questionnaire; EMR, electronic medical record.

Implementation outcome (alternate terms)	Definition (using EBP as the implementation)	Standard MBC Implementation (data source in brackets)	eMBC Implementation, in addition to those in standard MBC (data source in brackets)
Adoption (Uptake)	Initial action to try or employ an EBP	Proportion of physicians who record at least one PHQ-9 score in the chart (EMR/chart)	Proportion of patients who accessed the WeChat Easy to Recover from Depression mini-programs at least once (app, coach)
Penetration (Reach)	Integration of an EBP within a service setting and its subsystems	Proportion of patients with a PHQ-9 score recorded (EMR/chart)	Proportion of patients who accessed the WeChat Easy to Recover from Depression mini-programs at least twice (app); Proportion of patients who accessed at least 2 sessions of coaching (chart review, coach)
Fidelity (Adherence)	Degree to which an EBP was implemented as planned	Proportion of patients where a PHQ-9 score was used in a clinical decision (interviews)	Proportion of patients who completed 4 of 6 lessons in the Come Back program (app).
Acceptability (Satisfaction)	Perception of stakeholders that an EBP is agreeable or satisfactory	Evidence-Based Practice Attitude Scale (EBPAS) [39] (survey of physicians)	System Usability Scale [40] (survey of patients)
Appropriateness (Compatibility)	Perceived fit, relevance, or compatibility of the EBP	Qualitative exploration in physicians (interviews)	Qualitative exploration in patients (interviews)
Cost (Resources)	Cost impact of an EBP	Costs of MBC training program; estimated costs of workflow (based on Chinese sources)	Costs of eMBC elements, incl WeChat apps and coaching (based on Chinese sources)
Sustainability (Maintenance)	Sustained use and durability of an EBP	Qualitative exploration in physicians (interviews)	Qualitative exploration in patients (interviews)

The clinical outcomes are assessed at baseline, two months, four months, and six months (Table 2). The primary clinical outcome will be PHQ-9 remission rate (PHQ-9 score ≤ 4) at six months. Other clinical outcomes (scales) will include PHQ-9 change scores, anxiety symptom change scores (GAD-7), functional disability (SDS), quality of life (QOL-6 [41], EQ-5D-5L [42]), health economic assessment (HEA [43]), medical adherence (Patient Adherence Questionnaire, PAQ [44]) and doctor-patient alliance (Scale To Assess Therapeutic Relationships in Community Mental Health Care STAR-P, [45]).

**Table 2 TAB2:** Clinical outcomes and measures.

Outcome	Patient-Rated Scale
Depressive symptoms	Personal Health Questionnaire (PHQ-9) [6]
Anxiety symptoms	Generalized Anxiety Disorder (GAD-7) [30]
Functioning	Sheehan Disability Scale (SDS) [32]
Quality of life	Quality of Life scale (QOL-6) [41]; EuroQoL 5 Dimensions (EQ-5D) [42]
Medication adherence	Patient Adherence Questionnaire (PAQ) [44]
Doctor-patient alliance	Scale To Assess Therapeutic Relationships in Community Mental Health Care (STAR-P) [45]
Health services utilization	Health Economics Assessment (HEA) [43]

These patient-rated outcomes and basic demographic information will be collected from all patient participants via *eSmile*, a separate WeChat research outcomes mini-program created for this study. The *eSmile *mini-program includes a consent notice with each survey. A reminder notification will be automatically sent out to remind patients to complete the scales at scheduled dates, with a follow-up reminder after 24 hours if scales are not completed.

Economic outcomes will include health service utilization data (both mental health- and non-mental health-related) from the HEA and from available EMR/chart records, including health provider encounters, emergency room visits, hospitalizations, diagnostic tests, and prescriptions.

Sample size and data analysis

Sample Size

For the clinical outcomes, we will select 1200 participating patients, representing about 100 patients per clinic and about five patients per physician. The sample size of 240 physicians and 1200 patients (based on 12 clinics and 100 patients per clinic) will allow us to detect a minimal effect size between conditions with odds ratios of about 1.3 for categorical outcomes such as Implementation Reach and PHQ-9 remission rate, and about d=0.25 for continuous outcomes such as Implementation Acceptability (EBPAS scores) and patient functionality (SDS scores). These are regarded as small but clinically relevant effects; for comparison, these are similar to effect sizes found for comparisons of antidepressant medications versus placebo.

Data Analysis

We will use intent-to-treat samples for the analysis of implementation and clinical outcomes. Prior to the final data analysis, a full statistical analysis plan will be published. In summary, the statistical approach for dichotomous variables (e.g., proportion of patients with a documented PHQ-9 score; PHQ-9 remission rates) will use mixed-effects logistic regression models and for continuous variables (e.g., PHQ-9 and SDS scores at two-, four-, and six-month assessments) will use mixed-effects regression models, with compound symmetry covariance matrices to account for clusters created by clinics and longitudinal data, and adjusting for relevant (and especially equity-sensitive) baseline variables including age, sex, baseline severity, etc. These models belong to the Generalized Linear Mixed-effects Models (GLMMs) that are the most efficient and recommended statistical methods for analyzing clustered and longitudinal clinical trial data [46]. GLMM can account for data missing at random without requiring imputations of the missing values [47]. These analyses will allow us to examine main effects of cluster (e.g., potential differences in care quality between sites) and interaction effects between the two assigned conditions. Results will be reported as adjusted odds ratios, effect sizes (e.g., Cohen’s d) and 95% confidence intervals.

This study design will also allow us to conduct a secondary “piggy back” economic analysis [48] using health service utilization data from the HEA and EMR/charts. For example, the economic evaluation can model the cost-effectiveness of eMBC compared to standard MBC by estimating the incremental net benefit (INB) using net benefit regression [49], thereby allowing the statistical methods to be extended to a cost-effectiveness setting. In addition to creating a cost-effectiveness acceptability curve (CEAC), we will determine the incremental cost-effectiveness ratio (ICER).

We will also conduct mediational analyses using structural equation modelling to explore the factors that mediate the impact of the intervention condition on both clinician-and patient-level outcomes. For example, we can examine mediation effects by using eMBC fidelity as the dependent variable, the intervention condition as the independent variable, and contextual factors identified in Phase 1 as mediating variables. We will follow recommendations for assessing mediation in a multilevel context [50] based on factors at clinic, physician, and patient levels. The sample size projected for the cluster randomized evaluation will allow us to detect mediation effect sizes of about κ2=0.15 for clinician and patient models, which represent medium effect sizes [50].

In addition, we will employ a ‘mixed-methods sequential explanatory design,’ an analytic lens that assigns priority to quantitative data findings and uses them to guide and inform qualitative phases [51]. Purposive sampling will identify sites that show low fidelity to eMBC for further qualitative exploration. As in Phase 1, we will use Interpretive Description methods in subsets of physicians and patients to explore their contextual and motivational factors for standard MBC and eMBC adoption as well as reasons for deviation. Regardless of the specific methods, sufficient data collection (e.g., interviews, focus groups) will occur at purposefully selected [52] diverse low-fidelity sites in Shanghai to produce a rich ‘interpretive account’ [53] of the contextual factors that impact eMBC implementation.

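### With 600 patients and 120 physicians per arm, the stated detectable effects of OR 1.3 and, for physician EBPAS scores, d = 0.25 are out of reach even if clustering is ignored

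*Protocol article*

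**What the plan says.** The Sample Size section of the protocol article makes one numerical claim about what the trial can see. It starts from "The sample size of 240 physicians and 1200 patients (based on 12 clinics and 100 patients per clinic") and says that this will allow the trial to "detect a minimal effect size between conditions with odds ratios of about 1.3 for categorical outcomes such as Implementation Reach" and PHQ-9 remission. These are the two primary outcomes. For continuous measures it gives "about d=0.25 for continuous outcomes such as Implementation Acceptability (EBPAS scores) and patient functionality (SDS scores").

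Three other statements bear on the claim:

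- Materials and methods: "The unit of randomization was the mental health centre", and "We randomly allocated 12 mental health centres in Shanghai to two intervention groups". With 1:1 allocation that is 6 clinics per arm.
- Sample Size, on the clinical outcomes: "we will select 1200 participating patients, representing about 100 patients per clinic and about five patients per physician". That is 600 patients and 120 physicians per arm.
- Table 1 gives the source of the acceptability outcome as "Evidence-Based Practice Attitude Scale (EBPAS) [39] (survey of physicians"). EBPAS therefore has at most 240 respondents.

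The Data Analysis section plans mixed models that account for clinics, and 95% confidence intervals.

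**The concern.** One OR is claimed for both primary outcomes, and one d is applied to a physician survey (n = 240) and to a patient scale (n = 1200). Both figures are small for a trial with six randomized units per arm. If they were obtained without clustering, or with the patient count used for a physician outcome, the trial is presented as more sensitive than it is.

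The article describes these effects as small yet clinically meaningful and likens them to antidepressant-placebo differences. A reader who accepts that would take a null result on Reach or remission as evidence against effects of that size, when the trial would more often than not miss them. EBPAS is not a primary outcome, so less depends on it.

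**Working it through.** **Inputs from the article.** 12 clinics, 6 per arm; 600 patients per arm (m = 100 per clinic); 120 physicians per arm (m = 20 per clinic); target OR 1.3 and d = 0.25.

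**Assumed, because the article gives no value.** Two-sided 5% (in line with the planned 95% intervals); 80% power; control rates from 10% to 90%; clinic ICCs from 0 to 0.05; no attrition. Normal quantiles: 1.960 + 0.842 = 2.802.

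**1. Trying to reproduce OR 1.3, with ICC = 0.** For control rate p1, p2 = OR·p1 / (1 − p1 + OR·p1), and

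power = Φ{ [(p2 − p1)√n − 1.960·√(2p̄(1 − p̄))] / √[p1(1 − p1) + p2(1 − p2)] }.

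The most favourable case is p1 = 0.467, p2 = 0.533, a difference of 0.0655. With n = 600: (0.0655 × 24.49 − 1.960 × 0.7071) / 0.7056 = 0.31, and Φ(0.31) = 62%.

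Sample size for 80% power: [(1.960 × 0.7071 + 0.842 × 0.7056) / 0.0655]² ≈ 914 per arm, 1828 in total.

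| Control rate | Power for OR 1.3, 600 per arm | n per arm for 80% | Smallest OR at 80% |
|---|---|---|---|
| 20% | 47% | 1324 | 1.47 |
| 30% | 57% | 1037 | 1.41 |
| 47% (best case) | 62% | 914 | 1.38 |
| 80% | 41% | 1550 | 1.54 |

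A positive ICC can only lower these powers. The closest I can get to the stated figure is OR 1.33, using one-sided 5%, no clustering, no dropout and a rate near 50%.

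**2. EBPAS, 120 physicians per arm, ICC = 0.**

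- Detectable d = 2.802 × √(2/120) = 0.36.
- Power for d = 0.25: Φ(0.25/0.1291 − 1.960) = Φ(−0.02) = 49%.
- n for d = 0.25: 2 × (2.802/0.25)² ≈ 252 per arm.

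**3. SDS and similar patient scales, 600 per arm.** At ICC = 0 the detectable d is 2.802 × √(2/600) = 0.16, and power for d = 0.25 is 99%. The largest design effect that keeps 80% power at d = 0.25 is 600 × 0.25² / (2 × 2.802²) = 2.39. Since the design effect is 1 + 99·ICC, ICC can be at most 1.39/99 = 0.014. With t on 10 df (12 clinics − 2) the required noncentrality is 3.110 instead of 2.802. The limit is then 600 × 0.25² / (2 × 3.110²) = 1.94, so ICC can be at most 0.94/99 ≈ 0.009. This part of the claim reproduces, at an ICC of about 0.01.

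**4. Illustration with clustering.** Design effect 1 + (m − 1)·ICC, t on 10 df, 80% power, 50% control rate, no attrition. For the OR, solve (p2 − p1) / √{DE·[p1(1 − p1) + p2(1 − p2)]/600} = 3.110.

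| Assumed ICC | DE, m = 100 | Power for OR 1.3 | Detectable OR | Detectable d, SDS | DE, m = 20 | Detectable d, EBPAS |
|---|---|---|---|---|---|---|
| 0.01 | 1.99 | 31% | 1.66 | 0.25 | 1.19 | 0.44 |
| 0.02 | 2.98 | 22% | 1.87 | 0.31 | 1.38 | 0.47 |
| 0.05 | 5.95 | 13% | 2.44 | 0.44 | 1.95 | 0.56 |

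**5. Reach with more charts.** If Reach were counted in more than 100 charts per clinic, OR 1.3 would need about 153 charts per clinic at ICC = 0 (914/6). With unlimited charts in 12 clinics, and a rate near 50%, it would still need ICC ≤ 6 × [0.5·ln 1.3 / 2.802]² / 2 = 0.0066 (normal approximation).

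**The case against.** **Alpha and power are unstated, and the hypothesis is directional.** One-sided 5% without clustering gives OR 1.33, which could be rounded to 1.3. But that calculation ignores the randomization by centre and fits poorly with the planned 95% intervals. It also leaves EBPAS at d = 0.32.

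**Reach may not be limited to 1200 patients.** Materials and methods defines it over eligible patients by chart review, while the 1200 are selected for the clinical outcomes. This stands in part: a reader might infer that OR 1.3 is impossible for Reach whatever the denominator, and the article does not support that. With 300 charts per clinic and an ICC of 0.002, OR 1.3 would be detectable. But the Sample Size sentence ties the figure to 1200 patients, a larger denominator helps only with a very small ICC, and remission is confined to the 1200 in any case.

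**Covariate adjustment adds precision.** It is planned and I have not counted it. For remission it would have to do the work of about 314 further patients per arm (914 − 600) before any clustering. For EBPAS it would take a baseline correlation of about 0.72, and no baseline EBPAS is described.

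**The OR and the d seem to contradict each other.** A reader might infer this because the ICC of 0.014 that yields d = 0.25 for patient scales yields a detectable OR of 1.66. That is weak as a separate point: the outcomes differ and may have different ICCs, and nothing says that they share one.

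**A condensed article may leave inputs to the analysis plan.** Agreed. The absence of an ICC or a reference rate is not the point; the point is the figures that are stated. The promised adjusted odds ratios with 95% intervals will also show what a null result excludes, which limits the harm.

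**Conclusion.** The claim is wrong as written for two of its parts. At two-sided 5% and 80% power, OR 1.3 is not detectable with 600 v 600 patients even at ICC 0: power is at most 62% and the smallest detectable OR is 1.38 at best. This is firm for PHQ-9 remission, and holds for Reach if it is assessed in the 1200 patients. For EBPAS, d = 0.25 has 49% power at ICC 0, and the detectable d is 0.36.

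It is tempting to extend this to every figure in the sentence. For SDS that would be incorrect: d = 0.25 has 99% power before clustering and is lost only when the clinic ICC exceeds about 0.01.

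The results at ICC 0 depend on the assumed alpha and power, and not on any assumed ICC. The results with clustering also depend on ICCs and a 50% reference rate that are mine, and serve only to show the size of the problem.

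**What to change.** Withdraw the claims of OR 1.3 and of d = 0.25 for EBPAS. Restate the detectable effects in three lines: patient binary, patient continuous and physician outcomes. Each should use its own n, the design effect 1 + (m − 1)·ICC with m = 100 or m = 20, and about 10 df. For Reach, use the denominator that the chart review will actually have.

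The sponsor should compute these from its own ICC, reference rate and attrition, and show those inputs beside the results. The assumed ICCs of 0.01 to 0.05 above give OR of about 1.66 to 2.44, SDS d of about 0.25 to 0.44 and EBPAS d of about 0.44 to 0.56. These illustrate the order of magnitude and are not replacement text.

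The statistical analysis plan that the article promises before the final analysis is a natural place for the correction. It needs no extra patients and no change in conduct. The only cost is that the stated figures become less favourable.
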